### Trial design and setting

2.1

The research will be conducted at the Inner Mongolia Maternity and Child Health Care Hospital in China from March 2025 to September 2025, employing clinical reagent testing and internationally recognized scales for quantitative investigation.

The study population consists of families of children with PKU, who will be divided into two groups: Group A will be the mHealth intervention group, while group B was the control group. The intervention group will receive mobile health interventions through WeChat group chats. The control group, on the other hand, will simply get regular health education, which includes an oral presentation on PKU by a professional physician at the time of enrollment, educating the parents of PKU children on how to manage their diets low in phenylalanine. A printed handbook on PKU disease and daily management knowledge will also be given to them, but they won’t have access to online education and training, frequent reminders for monitoring, or online consultation services.

The intervention will last for 6 months, with clinical indicators, intelligence tests, and questionnaire surveys being conducted at baseline, as well as at 3 and 6 months after the start of the intervention to examine the effectiveness of the intervention on the health management of children with PKU. The flow chart of the study is shown in **Figure 3** and **Table 1**.

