**Figure 3 f3:**
[figure not shown]
Flow chart of patient recruitment and study implementation.

**Table 1 T1:** Timeline for study enrollment, intervention, and evaluation.

Study Period	Recruitment	Intervention		Follow-up
Timepoint	-T1	0M	3M	6M
ENROLMENT: eligibility screen	✓			
Informed consent	✓			
ASSESSMENTS: sociodemographic variables		✓		
Anthropometric variables		✓	✓	✓
Intellectual development variables		✓	✓	✓
PKU knowledge		✓	✓	✓
Parents’ compliance with health management		✓	✓	✓
Parents’ mental health variables		✓	✓	✓
Family environment variables		✓	✓	✓

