#### Stage 3: determine intervention content and implementation options—mobile health intervention based on the WeChat

2.6.3

Based on the analysis and selections from the previous two stages, and after comprehensively considering affordability, practicability, effectiveness acceptability, safety, and equity, the final decision is to utilize WeChat group chats for remote mobile health intervention. The group chat will incorporate the following four functions to achieve the seven interventions outlined in Stage 2:

*Health education module and real-time reminder function*. Through the WeChat group, educational materials in various formats (e.g., illustrations, videos) will be distributed weekly to provide PKU knowledge and health education. Topics include basic disease knowledge, the importance of health management, low-Phe diets, and regular follow-up monitoring. Personalized reminder notifications will also be set up to encourage timely completion of dietary records and regular medical check-ups.
*Diet uploading and phenylalanine content query function*. Parents will input the types and quantities of food consumed by their child each day into the WeChat group chat. The system will automatically calculate the daily Phe intake, notify parents if the intake exceeds the recommended limit, and provide adjustment suggestions. Additionally, the WeChat group will include a built-in food Phe database containing Phe content for common foods across three meals, along with recommended low-Phe meal combinations.
*Regular feedback and incentive mechanism*. The group chat will record the dietary logs and compliance status uploaded by parents. At the end of each month, virtual rewards such as badges and titles will be issued based on the monthly records to motivate parents to continue maintaining healthy management behaviors.
*Family interaction and online consultation function*. Parents can interact with other PKU families in the group chat to share health management experiences. Additionally, the group chat will offer an online consultation feature, allowing parents to seek advice from professional physicians in the group at any time.

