### Outcomes

2.8

Primary Outcomes:serum phenylalanine and tyrosine levels in children with PKU.

Secondary Outcomes:

Nutritional indicators: Height/length (cm), weight (kg), head circumference (cm), the concentration of hemoglobin, prealbumin, albumin, complete blood count (red blood cells, white blood cells, platelets), serum iron, ferritin, and 25-Hydroxy vitamin D3.Intellectual development indicators: For children aged ≤6 years, professional physicians will use the 0–6 Years Child Developmental Behavior Assessment Scale for evaluation. For children aged >6 years, IQ will be assessed using the Chinese version of the Wechsler Intelligence Scale for Children, Fourth Edition (WISC-IV).

In addition, considering that the health management of children with PKU may impose psychological and quality-of-life burdens on their parents’ caregivers (37, 38), the study also focuses on the following indicators for parents’ caregivers: PKU disease knowledge, compliance, mental health, family health, and family atmosphere, etc. Specific details are as follows:

Changes in PKU knowledge.Changes in parental compliance with health management: Measured by the number of dietary Phe concentration logs and the number of blood tests during the intervention period (39).Impact of health management on parental mental health: Includes levels of anxiety and depression, self-efficacy, and parenting stress.Changes in the family environment of PKU children: Includes specific behavioral changes such as family communication and broader indicators such as family health.

Socio-demographic variables will be collected from patients at baseline. Clinical reagent testing and questionnaires will be conducted at baseline as well as at 3 and 6 months of follow-up, with data collection times shown in **Table 2**.

**Table 2 T2:** Data collection components and collection timeline.

Type of research	Data collection		Timepoint		
			0M	3M	6M
Quantitative research	Sociodemographic variables	Gender, age, parental education level, parental occupation, monthly household income per capita, only-child status, presence of other PKU patients in the family	✓		
	Anthropometric variables	Serum phenylalanine(Phe)and tyrosine(Tyr)levels, height/length (cm), weight (kg), head circumference (cm), the concentration of hemoglobin, prealbumin, albumin, complete blood count, serum iron, ferritin, and 25-Hydroxy vitamin D3	✓	✓	✓

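### The diet-log count in the compliance outcome comes from a tool given only to the intervention arm, and the compliance measure as defined has no baseline to change from

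*Protocol article*

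**What the plan says.** Section 2.8 (Outcomes) lists, among the caregiver indicators, "Changes in parental compliance with health management", and defines it as "Measured by the number of dietary Phe concentration logs and the number of blood tests during the intervention period". Table 2 repeats the definition and ticks it at 0M, 3M and 6M. Table 1 ticks the row "Parents’ compliance with health management" at the same three times.

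Section 2.6.3 describes how logs arise: "Parents will input the types and quantities of food consumed by their child each day into the WeChat group chat". The system then calculates daily Phe intake, families are reminded to complete their records, and virtual rewards are issued monthly from those records. On capture it says "The group chat will record the dietary logs and compliance status uploaded by parents".

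Section 2.1 assigns this tool to one arm: "The intervention group will receive mobile health interventions through WeChat group chats". Controls receive an oral presentation and a printed handbook, and they "won’t have access to online education and training, frequent reminders for monitoring, or online consultation services".

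Section 3 (Statistical analysis) plans a Mann-Whitney U test, for each indicator, of the change from baseline at 3 and at 6 months.

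**The concern.** Two separate faults meet in this outcome.

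First, uploading a diet log is a component of the intervention. A between-arm comparison of log counts then largely records who was given the logging tool. It could be significant with no difference in how families manage the diet.

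Second, a count over the intervention period cannot exist at 0M, because the intervention starts only after consent (section 2.2) and no look-back window is given. The planned change from baseline therefore has nothing real to subtract.

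The second of the two specific objectives in the Introduction is effectiveness in improving health behaviour management. Compliance is the outcome that directly counts what parents do to manage PKU. A significant result on the log count would be read as evidence of behaviour change, and the Discussion foresees extending an effective programme to other regions.

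**Working it through.** **Plan's own figures.** No rate, count or power is stated for compliance, so there is nothing to reproduce for it. The sample size in section 2.3 concerns serum Phe (360 v 260 μmol/L, SD 100, two-sided α = 0.05, power 90%). A two-sample t-test solves at n = 22.02, hence 23 per group as stated. It serves here only to fix the arm sizes: 25 enrolled per arm, and 25 × 0.9 = 22.5, so about 22 completers.

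**Step 1: access to logging.**

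| | Intervention | Control |
|---|---|---|
| Where logs are entered | WeChat group chat (2.6.3) | none described |
| Who records them | the group chat (2.6.3) | none described |
| Reminders to complete dietary records | yes (2.6.3) | none described |
| Rewards based on the records | yes (2.6.3) | none described |

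**Step 2: size if control logs are all zero (assumption).** Let *k* of *N* intervention families upload at least one log, with distinct counts, and let every 0M value be 0. The Mann-Whitney statistic departs from its null mean by *kN*/2. With *t* = 2*N* − *k* tied zeros, its variance is (*N*²/12) × [(2*N* + 1) − (*t*³ − *t*)/(2*N*(2*N* − 1))]. With continuity correction, z = (*kN*/2 − 0.5)/SD.

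- *N* = 25, *k* = 4: departure 50; *t* = 46; variance 52.083 × (51 − 39.710) = 588.0; SD 24.25; z = 49.5/24.25 = 2.04; P = 0.041.
- *N* = 22, *k* = 4: departure 44; *t* = 40; variance 40.333 × (45 − 33.805) = 451.5; SD 21.25; z = 43.5/21.25 = 2.05; P = 0.041.
- *k* = 3 gives P = 0.081 at either size.
- All 25 uploading gives P of about 1 × 10⁻¹⁰; all 22 gives about 1.4 × 10⁻⁹.

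At 25 per arm, the chance of P < 0.05 for a given true share of families who ever upload is the binomial probability of *k* ≥ 4:

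| Share who ever upload | Chance of P < 0.05 |
|---|---|
| 10% | 24% |
| 20% | 77% |
| 30% | 97% |
| 50% | over 99.9% |

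**Step 3: range if some controls do log (assumption).** Reduce each family to any log or none, with *c* control families logging. The departure becomes (*k* − *c*)*N*/2, and both tied groups enter the variance. At *N* = 25, the smallest *k* giving P < 0.05 is:

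| Controls logging (*c*) | Intervention families needed (*k*) | P |
|---|---|---|
| 0 | 4 | 0.041 |
| 1 | 6 | 0.045 |
| 2 | 8 | 0.037 |
| 5 | 12 | 0.040 |

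For example, with *c* = 2 and *k* = 8 the departure is 75, the tie term is (990 + 63,960)/2,450 = 26.51, and the variance is 52.083 × 24.49 = 1,275.5. The SD is 35.71, so z = 74.5/35.71 = 2.09. The threshold thus depends strongly on what controls can do, which the article does not state.

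**Step 4: the baseline.** The definition covers the intervention period, both tables tick 0M, and section 3 subtracts the 0M value. At 0M no intervention time has elapsed, so the value is 0 for every family or is undefined. If it is 0, the change equals the follow-up count and the subtraction does nothing.

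**The case against.** The strongest reply is that zero logging among controls is not in the text. The outcome counts dietary Phe logs, not WeChat uploads. The list of things withheld from controls does not mention diet logging, and they are taught low-Phe diet management. A paper diary for controls is a detail an article may leave to the full protocol. This stands: a reader might infer that the control count is zero by design, but the article supports that only as an inference, and the figures in step 2 are conditional on it. It does not rescue the comparison, because a paper diary without reminders, automatic calculation or rewards is a different instrument from the group chat.

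A reader might also infer that the whole compliance outcome shows only who received the tool. The documents do not support that. Both arms can have blood tests, and more testing after reminders would be a genuine effect of the intervention. The article does not say that the two counts are added together.

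Third, the baseline fault may have little inferential effect. If every 0M value is 0, the Mann-Whitney result is the same with or without the subtraction. That is right. The definition, the schedule and the analysis still contradict one another and need reconciling, but this is not a separate source of bias.

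Finally, this is one of several caregiver indicators, and the behavioural objective is also informed by knowledge, self-efficacy, family communication and family health. This stands too, and it limits the weight of the point.

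**Conclusion.** The point holds for the dietary-log count. As the article describes it, logging is prompted, calculated, recorded and rewarded in one arm only, so a between-arm test of log counts reflects access to the tool. Assuming that controls log nothing, 4 of 25 (16%) or 4 of 22 (18%) intervention families uploading anything is enough for P = 0.041. If some controls log by another route the threshold rises, for instance to 8 of 25 when 2 controls log, but the arms are still measured by different means.

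The baseline point holds as an internal contradiction: a count over the intervention period has a 0M value that is zero or undefined, so the planned change score has no meaningful baseline.

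The first fault does not reach the blood-test count, provided the two counts are analysed separately. The outcome is secondary, and neither the primary outcome nor the sample size is affected.

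**What to change.** 1. Report WeChat log counts for the intervention arm only, as uptake of the intervention, with no between-arm test.
2. Make the between-arm compliance outcome the number of blood Phe tests per child over months 0-3 and months 0-6. Exclude the scheduled study-visit tests, which both arms have by protocol.
3. Capture those tests in the same way in both arms, including tests at local institutions. Section 2.6.2 places regular Phe monitoring there, so the trial hospital's records alone may miss some.
4. Remove the 0M tick for this measure in Tables 1 and 2, and drop its change-from-baseline test. A pre-enrolment test count may be used only as a covariate, in a regression model for counts, and only where a full look-back window exists. Children are eligible from age 0, so the youngest infants will not have one.

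The cost is small. Log counts are no longer a comparative result, and both arms need a common way to record test dates. No extra participants or study visits are required.

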### Questionnaires

2.9

Socio-demographic and clinical data will be collected using self-designed questionnaires and the medical record system. Socio-demographic variables included gender, age, parental education level, parental occupation, monthly household income per capita, only-child status, and presence of other PKU patients in the family. Clinical variables included age at diagnosis, historical serum Phe concentrations, and intellectual development level.

Changes in PKU knowledge will be assessed using a self-designed PKU theory scale. This scale is adapted from the study conducted by Öztürk F et al. on the PKU knowledge of parents (40). It comprises 10 questions related to PKU, all of which are based on the information provided in Nelson’s textbook Classical Pediatrics to assess both correct and incorrect knowledge. Each question is scored as 1 point, with the total score ranging from 0 to 10. The development of the scale will be undertaken by the researcher, who will also complete its final validation. To determine the appearance validity and content validity, a pre-test will be administered to 20 randomly selected participants who did not take part in the final trial. These participants will be chosen from the recruited pool. The scale will be refined through pre-testing and expert review to ensure its robustness and reliability.

Depression and anxiety will be assessed using an ultra-brief screening scale for anxiety and depression (PHQ-4), which is a short, self-report scale used to assess an individual’s symptoms of depression and anxiety over the past 2 weeks (41). The scale comprises two dimensions: depression and anxiety, with a total of four items. The first two items assess depressed mood, while the last two evaluate anxiety. Each item is rated on a 4-point scale, with “not at all”, “a few days”, “more than half the days” and “almost every day,” corresponding to a score of 0, 1, 2, and 3, respectively, and the total score ranges from 0 to 12. Different levels of psychological problem were defined with scores: normal (0~2), mild (3~5), moderate (6~8), and severe (9~12). The Cronbach’s alpha of the PHQ-4 was 0.865, which is of high validity and reliability, in a study conducted in Chinese parents (42). Due to its brevity and efficiency, the PHQ-4 is a practical tool for healthcare professionals to quickly and effectively assess anxiety and depression in target populations.

Self-efficacy will be assessed by New General Self-Efficacy Scale-Short Form (NGSES-SF). The NGSES was first developed by Chen, G. to measure individuals’ perception of their ability to perform across a variety of different situations in 2001. Wang Fei et al. later adapted the short form (NGSES-SF) and validated its reliability and validity in a Chinese population (43). The NGSES-SF is a 3-item, 5-point Likert-type scale, with responses ranging from 1 (very disagree) to 5 (very agree). Higher scores indicate a greater level of self-efficacy.

Parenting stress will be measured by the Parenting Stress Index (PSI-SF-15) and the Guilt about Parenting Scale (GAPS).The PSI was first developed by Abidin to measure parenting stress perceived by the caregivers in 1995 (44). Jie Luo et al. (45) later adapted the short form (PSI-SF-15) and validated its reliability and validity in Chinese parents. The PSI-SF-15 comprises three dimensions: parental distress (PD), parent-child dysfunctional interaction (PCDI), and difficult child (DC). It is a 5-point Likert-type scale with 15 items, ranging from 1 (very disagree) to 5 (very agree), with higher scores indicating a higher degree of parenting stress perceived by caregivers. The Guilt about Parenting Scale (GAPS) was developed by Haslam et al. in 2019, to measure the degree of guilt caused by conflicts between parents’ work and family responsibilities (46). It consists of 10 items, scored from 1 (completely disagree) to 7 (completely agree), all with positive scoring, and higher scores indicate a higher level of parental parenting guilt. After verification, the Cronbach’s α of this scale was 0.89, indicating good reliability and validity.

Family health will be measured by the A Short Form of the Family Health Scale (FHS-SF), which mainly includes four dimensions of family/social and emotional health processes, family healthy lifestyles, family health resources, and social support outside the family. It is used to comprehensively assess the family health status. To reduce subjects’ fatigue responses and increase the completion rate in practical studies, Crandall et al. further developed the short form of the Family Health Scale (47). The scale consists of ten items, and the response options are usually on a five-point scale ranging from “strongly disagree” to “strongly agree”. Among them, the three items of the family health resource dimension are reverse-scored. Fei Wang et al. adapted the Chinese version of the FHS-SF based on this, with Cronbach’s α of 0.83, which is of high validity and reliability, in a study involving the Chinese population (48).

Family communication will be assessed by A Short Form of the Family Communication Scale (FCS-SF), which has four items measuring a single dimension: family communication level. It is a 4-point Likert scale, with responses ranging from 1 (strongly disagree) to 4 (strongly agree).The Family Communication Scale has demonstrated good internal consistency and reliability in the localization process in Greece (49), Spain (50) and China (51). To facilitate quicker and more convenient use in research and clinical practice, Siyuan Fan et al. developed the FCS-SF based on the FCS-10. The FCS-SF retains the psychometric advantages of the FCS-10 while being simplified to assess the overall level of family communication more efficiently. It has shown good psychometric properties in Chinese populations, with a Cronbach’s α of 0.917.

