### Sample size

2.3

The sample size was calculated based on the primary metabolic indicator, serum Phe concentration. This study is a randomized controlled trial, with the intervention group receiving mobile health interventions and the control group receiving regular health education. The sample size ratio between the two groups is 1:1. According to a randomized controlled trial on PKU children based on a mobile health app (35), the blood Phe concentration in the control group was 360 μmol/L, while that in the intervention group was 260 μmol/L, with a standard deviation of 100 μmol/L in both groups. Using a two-tailed test with α = 0.05 and β = 0.1, the power (1-β) was set at 90%. Calculations performed using PASS 15 indicated that a minimum of 23 participants per group was required. Accounting for a 10% attrition rate, each group was expanded to 25 participants, resulting in a total minimum sample size of 50 participants.

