## Statistical analysis

3

Statistical analysis will be performed using SPSS Statistics 26.0. Categorical data will be expressed as counts and percentages (n, %). Continuous data will be presented as mean ± standard deviation (x¯ ± s). The Mann-Whitney U test will be used to compare changes in each indicator between the two groups at 3 months and 6 months post-intervention relative to baseline. The Wilcoxon test will be employed to compare differences between the two groups at baseline and across four follow-up time points. Baseline demographic characteristics between the two groups will be compared using the chi-square test. A two-tailed test will be applied, and a P-value < 0.05 will be considered statistically significant.

If a reasonable amount of missing data is present, the data summary will indicate that the data are missing at random. In such cases, all analyses will incorporate multiple imputation procedures using baseline variables as auxiliary variables to address missing data. Linear regression and logistic regression will be selected for the imputation process, and the final analysis results will be combined to complete the imputation and analysis procedures.

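### The Phe comparison uses an unadjusted change from the single 0M time point and gives the collected historical Phe no role, which leaves avoidable baseline noise in a trial of about 45 evaluable children

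*Protocol article*

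**What the plan says.** All references are to the protocol article.

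- **Primary outcome (section 2.8):** "serum phenylalanine and tyrosine levels in children with PKU".
- **Timing (section 2.8, Table 2):** "Clinical reagent testing and questionnaires will be conducted at baseline as well as at 3 and 6 months of follow-up". Table 2 has one tick for Phe and Tyr at each of 0M, 3M and 6M.
- **Between-group test (section 3):** the Mann-Whitney U test is used to "compare changes in each indicator between the two groups at 3 months and 6 months post-intervention relative to baseline". No covariate is named. Baseline variables are mentioned only as auxiliaries for multiple imputation.
- **Historical data (section 2.9):** "Clinical variables included age at diagnosis, historical serum Phe concentrations, and intellectual development level". They come from questionnaires and medical records. The number of readings, their dates, the laboratory and diet status are not given, and Table 2 does not list them.
- **Sample size (section 2.3):** "The sample size was calculated based on the primary metabolic indicator, serum Phe concentration". The inputs are means and an SD of the Phe level. No SD of change and no within-child correlation appear.

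**The concern.** A raw change score carries the full noise of the 0M reading into the outcome. Recent intake, sampling and assay variation at that one time point are subtracted from every child's follow-up value. Two remedies are available without further blood samples: adjust for 0M Phe instead of subtracting it, and use the historical Phe that is collected anyway. The stated comparison does neither.

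The plan allows for 50 children and 10% attrition, so about 45 are evaluable. At that size, lost efficiency can decide whether the planned difference of 100 μmol/L is detected. The sample size uses the SD of the level while the test is on change, so the planned power holds for the change score only if r is about 0.5 or higher.

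**Working it through.** **Inputs from section 2.3.** Control: "the blood Phe concentration in the control group was 360" μmol/L. Intervention: "while that in the intervention group was 260" μmol/L, so the difference is 100. Both arms: "with a standard deviation of 100" μmol/L. Two-sided α is 0.05, power 90%, 23 per arm, raised to 25 for attrition.

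**The plan's own figure.** Normal approximation: n = 2(1.960 + 1.282)² × (100/100)² = 21.0, rounded up to 22. The two-sample t-test gives 22.02, hence 23. The stated 23 is reproduced. Evaluable: 25 × 0.9 = 22.5 per arm, so I use 22.

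**Assumptions not in the documents.** Readings within a child are exchangeable with SD 100 and correlation r. The baseline is the mean of k readings: 0M plus k − 1 historical.

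**Variance of change**, in units of 100²:

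Var = 1 + [1 + (k − 1)r]/k − 2r = (1 − r)(1 + 1/k)

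Relative to k = 1 this is (k + 1)/(2k), whatever r is: 0.75 for k = 2, 0.67 for k = 3, 0.625 for k = 4. With k = 1 the SD of change is 118 at r = 0.3, 100 at r = 0.5 and 77 at r = 0.7. It exceeds the planned 100 whenever r is below 0.5.

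**Power of the planned Mann-Whitney test on change** (simulated, 22 per arm, difference 100):

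| r | k = 1 | k = 2 | k = 3 | k = 4 |
|---|---|---|---|---|
| 0.3 | 0.76 | 0.87 | 0.90 | 0.92 |
| 0.5 | 0.89 | 0.95 | 0.97 | 0.98 |
| 0.7 | 0.98 | 1.00 | 1.00 | 1.00 |

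**Incomplete history.** If half the children have only 0M and the rest have two to four readings in all, power goes from 0.76 to 0.83 at r = 0.3, from 0.89 to 0.93 at r = 0.5 and from 0.98 to 0.99 at r = 0.7.

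**Correlation that decays with time** (readings at 0, −1, −2 and −3 months, outcome at +6). With 30% of variance as reading-to-reading noise, the variance of change falls from 1.19 to 0.93, from 1.256 to 1.052 and from 0.895 to 0.652 in three settings. With no such noise it rises slightly, from 0.937 to 0.967 (power 0.90 to 0.89).

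**Noisier history.** At r = 0.5 and 23 per arm, averaging in two historical readings with twice the SD raises the SD of change from 100 to 111-126. The t-test power drops from 0.91 to 0.75-0.85.

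**How much comes from not adjusting.** Residual variance after adjusting follow-up Phe for 0M is 1 − r². After adding h exchangeable historical readings, with m = h + 1, it is 1 − m·r²/[1 + (m − 1)r].

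| r | change from 0M | adjusted for 0M | adjusted for 0M and two historical |
|---|---|---|---|
| 0.3 | 1.40 | 0.91 | 0.83 |
| 0.5 | 1.00 | 0.75 | 0.625 |
| 0.7 | 0.60 | 0.51 | 0.39 |

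At r = 0.3, adjusting for 0M alone (0.91) already does better than change from a mean of three readings (0.7 × 4/3 = 0.93). Adjustment also tolerates poor history, because the historical mean gets its own slope. At r = 0.5, two historical readings that correlate only 0.3 with 0M and follow-up, and 0.5 with each other, give 0.72 against 0.75 without them, whatever their SD.

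**The case against.** The strongest reply is that nothing here is an error. Change from the pre-intervention visit is common, and the exact definition of baseline is often left to an analysis plan. That stands in part: the comparison is valid. But section 3 does state the test and its outcome, so its efficiency can be judged as written.

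The second reply also stands. The documents do not show that usable history exists. The values are listed beside age at diagnosis and may be largely diagnostic. Section 2.2 admits children from age 0, who may have no on-diet history. Section 2.6.1 describes poor follow-up compliance, and section 2.6.2 places monitoring in local institutions, so readings may be sparse and come from several laboratories. A reader might infer that several readings per child are in hand and that a four-reading baseline is worth 60% more patients (1/0.625 = 1.6). The documents do not support that: it needs three recent, exchangeable historical readings for every child.

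Third, much of the loss at low r comes from not adjusting rather than from having one reading. That is right, and it changes the preferred fix.

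A reader might also infer that pre-randomisation values cannot introduce bias. This holds only for a fixed selection rule. Section 3.1 has hospital physicians gather all data, and deciding which readings count as recent and on-diet takes judgement.

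Finally, Table 2 does not literally limit 0M to one blood sample, and historical Phe might serve as an imputation auxiliary. Neither gives it a role in the comparison itself.

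**Conclusion.** The point holds as one of efficiency, not validity. The stated Phe comparison leaves avoidable baseline noise in the outcome, and pre-randomisation data on the same analyte have no stated part in it.

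The gain is material if r is about 0.3 (11 to 16 points of power with one to three usable historical readings for every child), moderate at 0.5 (6 to 9 points) and small at 0.7. It is roughly halved if half the children have no usable reading. Simple averaging can gain nothing or lose power if the readings are much more variable or if there is no reading-to-reading noise. These figures rest on an assumed r, an assumed number of readings and a normal exchangeable model.

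It does not follow that the trial is underpowered. At r = 0.5 the planned test has about 0.89 power with 22 per arm, close to the 90% target.

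**What to change.** Before unblinding, pre-specify that follow-up Phe is compared between arms with adjustment for 0M Phe and for the mean of the most recent on-diet historical serum Phe readings in a fixed window before enrolment, using ANCOVA or its rank version. An example rule is 6 months, at most three readings, diagnostic pre-diet values excluded, and the 0M value used where no reading qualifies. Select the readings by that rule before the abstractor knows the allocation.

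If the change score is kept, define baseline as the mean of 0M and those readings, and report the 0M-only change as a sensitivity analysis.

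Add historical Phe, with dates, to the baseline column of Table 2.

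The cost is a few sentences in section 3 and one table entry, with no extra children, visits or blood samples. There are two small drawbacks. The number and source of historical readings will vary between children. No historical Tyr is listed, so the Tyr analysis would adjust for 0M Tyr only.
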